#### Objective 3: to explore potential factors contributing to the benefits of mindfulness practice for patients with chronic CRP

1.3.2

Specifically, pre- to post-VRGM changes in pain will be described in relation to levels of immersion and presence in the VR experience, trait mindfulness, and amount of VRGM practice.

#### Objective 4: to understand cancer survivors’ experiences with VRGM

1.3.3

Participants will take part in in-depth, semistructured interviews to evaluate the acceptability and perceived benefits of VRGM, and to identify obstacles and facilitators of adherence and the challenges faced in initiating and maintaining VRGM practice.

## Methods

2

### Design

2.1

#### Overview

2.1.1

This study will employ a prospective, single-arm, pretest-posttest, mixed methods design. Adults with chronic CRP will participate in a 6-week home-based VRGM intervention with a one-to-one interview upon intervention completion.

### Participants

2.2

#### Sample size

2.2.1

This protocol is designed as a mixed methods feasibility study. The recruitment goal is 15 participants, a sample which is comparable to other mindfulness studies primarily focusing on feasibility, reporting sample sizes of 13–19 participants (39, 40). This sample size can allow the evaluation of feasibility outcomes by providing crucial information about the ability to recruit this population to such an intervention, intervention safety, adherence, and study completion rates. Feasibility will also partly be determined by participants’ attitudes toward VRGM and level of satisfaction with the intervention during the semistructured interviews.

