**Methods:**

This mixed methods feasibility study will employ a single-arm, pretest-posttest design with semistructured interviews. In total, 15 cancer survivors will be enrolled in a 6-week home-based intervention that consists of 10–15 min of daily VRGM practice. The primary outcome is feasibility as assessed by accrual rates, retention in the study, intervention adherence, questionnaire completion, and side effect rates. Participants will be assessed on psychosocial outcome measures (i.e., pain, sleep, depressive and anxiety symptoms, fatigue, quality of life, and mindfulness) before and after the intervention, and 6 weeks post intervention (follow-up). Changes in pain will be described in relation to levels of immersion and presence in the virtual environment, trait mindfulness, and amount of VRGM practice. Qualitative information will provide subjective detail on participants’ experience with VRGM to complement quantitative data. This study has been approved by the Health Research Ethics Board of Alberta Cancer Committee (HREBA.CC-20-0411).

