#### Quantitative analysis

2.9.1

Descriptive statistics will be used to calculate accrual rates (and reasons for not consenting to the trial), retention in the trial, intervention adherence, questionnaire completion, and adverse event rates (objective 1). Means and SDs will be calculated for continuous variables and frequency distributions for categorical variables. The profile of each outcome (means and SDs) will be displayed to visualize the pattern of changes over time (objective 2). Effect sizes and confidence intervals of changes in scores for outcome measures (i.e., pain, sleep, fatigue, depressive and anxiety symptoms, and quality of life) will be described across different time points (objective 2). Exploratory analyses will be used to describe the strength of associations of pre- to post-VRGM pain changes with the levels of immersion and presence in the VR experience, total amount of VRGM practice, and change in pre- to post-VRGM trait mindfulness (objective 3).

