### Strengths and limitations of this study

3.1

A strength of this study is employing a mixed methods design, which can enhance the rigor of the study by including findings from different methodological perspectives. This study has and will continue to involve patient research partners throughout the project to guide research questions, design, and implementation, and add context to the research findings. This study will provide the foundation needed to design and conduct a larger study to examine the efficacy of VRGM in improving chronic CRP. A limitation of this study is its single-group design, which is necessary to evaluate the acceptability of VRGM by as many cancer survivors as possible. This feasibility study is not statistically powered to evaluate the intervention efficacy for clinically relevant outcomes.

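### No primary feasibility rate has a pre-set value that counts as feasible, and confidence intervals are planned for the secondary symptom changes but not for the primary rates

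*Protocol article*

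**What the plan says.** The Abstract (Methods) defines the primary outcome: "The primary outcome is feasibility as assessed by accrual rates, retention in the study, intervention adherence, questionnaire completion, and side effect rates".

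Section 2.2.1 sets the size: "The recruitment goal is 15 participants". It supports this as "a sample which is comparable to other mindfulness studies primarily focusing on feasibility", with cited sizes of 13 to 19. It then says: "This sample size can allow the evaluation of feasibility outcomes by providing crucial information about the ability to recruit this population", and extends this to "intervention safety, adherence, and study completion rates". It adds that interview attitudes and satisfaction will partly determine feasibility.

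Section 2.6 describes the logs, device data and weekly contacts from which the rates will be calculated. It gives no target for any of them.

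Section 2.9.1 treats the two objectives differently. For the primary objective: "Descriptive statistics will be used to calculate accrual rates (and reasons for not consenting to the trial), retention in the trial", followed by adherence, questionnaire completion and adverse events. For the secondary objective: "Effect sizes and confidence intervals of changes in scores for outcome measures".

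On the use of the result, section 3.1 says: "This study will provide the foundation needed to design and conduct a larger study".

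**The concern.** The study promises to evaluate feasibility and to use the answer as the basis for a larger trial. An evaluation needs something to be evaluated against. As written, there is no target for accrual or retention, no minimum share of daily sessions that makes a participant adherent, no acceptable level of questionnaire completion or side effects, and no rule for combining them.

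The analysis section also attaches uncertainty to the uncontrolled symptom changes, which are secondary, and names none for the rates that carry the primary conclusion. A bare 80% retention or 0% side effects from 15 people gives a reader no idea how far the truth could lie from it. The choice of what to call feasible would be made with the results in view.

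**Working it through.** **Inputs.** n = 15 (section 2.2.1). The intervention is one session a day for 6 weeks (section 2.4), so 7 × 6 = 42 sessions per person. The article states no expected rate, precision target, threshold or dropout allowance, so there is no calculation behind 15 to reproduce.

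**Step 1. Precision of a person-level rate.** The exact (Clopper-Pearson) 95% interval for x out of n runs from the 2.5% quantile of Beta(x, n − x + 1) to the 97.5% quantile of Beta(x + 1, n − x).

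| Observed | Rate | Exact 95% interval |
|---|---|---|
| 9/15 | 60% | 32% to 84% |
| 11/15 | 73% | 45% to 92% |
| 12/15 | 80% | 52% to 96% |
| 13/15 | 87% | 60% to 98% |
| 15/15 | 100% | 78% to 100% |

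The Wilson interval for 12/15 is 55% to 93%, so the method matters little. The intervals are asymmetric: for 12/15 the limits lie 28 points below and 16 points above the estimate, so a single plus-or-minus figure would misdescribe them.

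**Step 2. Side effects.** With 0/15 the two-sided upper limit is 1 − 0.025^(1/15) = 21.8%, and the one-sided 95% bound is 1 − 0.05^(1/15) = 18.1%. The chance that a side effect with true rate p never appears is (1 − p)^15: 86% for p = 1%, 46% for p = 5% and 21% for p = 10%.

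**Step 3. Why the cut-off must be set in advance.** The cut-offs here are illustrative assumptions; neither is in the article. The entries are P(X ≥ r) for X ~ Binomial(15, p).

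| True rate | r = 9 | r = 12 |
|---|---|---|
| 60% | 0.61 | 0.09 |
| 70% | 0.87 | 0.30 |
| 80% | 0.98 | 0.65 |
| 90% | 1.00 | 0.94 |

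At a true rate of 60%, the chance of a favourable conclusion is 61% or 9% depending only on which cut-off is used. The table also shows that 15 people can support a useful rule, provided it is chosen beforehand.

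**Step 4. Denominators.** The calculations above apply to one yes/no result per participant.
- Accrual is computed from the numbers approached, referred, contacted and consented (section 2.6), so its denominator is not 15.
- Sessions and questionnaires are repeated within people. Pooling gives up to 15 × 42 = 630 sessions, but they come from 15 people and are not independent.
- Consented participants scoring above 20 on the Simulator Sickness Questionnaire do not continue (section 2.3.2), and the article does not say how they are counted. As a hypothetical case, if 2 of 15 consented people stop there and 11 complete, retention is 11/15 = 73% or 11/13 = 85%.

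**The case against.** The strongest reply is that this is a condensed article. The full protocol and analysis plan are not shown, descriptive statistics do not exclude intervals, and an analysis plan could add them. That weakens the point about intervals but does not remove it, because this text does specify intervals for the secondary outcomes and not for the primary ones. It has less force against the missing criteria. What counts as success on the primary outcome is protocol content, and the article has a section devoted to feasibility evaluation that is silent on it.

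A second reply is that formal progression rules are a preference in a first-step, mixed-methods study where interviews also inform the judgement. Interviews can qualify a pre-set band, but they do not replace one.

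Several stronger readings are tempting and are not supported:
- A reader might infer that n = 15 is wrongly justified. Section 2.2.1 claims no particular precision, section 3.1 disclaims power for efficacy, and 15 is a reasonable size for feasibility.
- A reader might infer that the lists of feasibility components contradict each other, since Objective 1 omits questionnaire completion. That list is worded as non-exhaustive, and the Abstract and section 2.9.1 name the same five components.
- A reader might infer that satisfaction is mentioned only in the sample size section. Section 2.3.3 also makes it an interview topic.
- A reader might infer that no criteria exist anywhere. The article can show only that it states none.

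**Conclusion.** The point holds in limited form. The article makes feasibility primary, sets no value for any primary rate that would count as feasible, and names intervals only for secondary outcomes. Followed as written, the feasibility conclusion rests on nothing fixed in advance.

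For person-level rates the unstated uncertainty is large. Intervals for observed rates from 60% to 80% are about 44 to 52 points wide, and an absence of side effects cannot exclude a true rate of about one in five. These figures assume 15 independent participants with one yes/no result each; they do not apply to accrual or to pooled sessions or questionnaires. The cut-offs of 9 and 12 are examples and say nothing about what the investigators should require.

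**What to change.** **Section 2.9.1.**
- Report exact 95% confidence intervals for the person-level primary proportions: retention, participants meeting a stated adherence minimum (a share of the 42 sessions), and participants with any side effect.
- For accrual, use the number approached or referred as the denominator.
- Summarise session and questionnaire completion per participant rather than pooling across participants.

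**Section 2.6.** Before enrolment, fix go/amend/stop bands for the five components named in the Abstract and section 2.9.1. Give each its denominator, including how participants stopped for a Simulator Sickness Questionnaire score above 20 are counted. Say how the interview findings will be weighed alongside the bands.

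**Section 2.2.1.** State the precision that 15 people give for person-level rates, for example 52% to 96% for 12/15, and an upper 95% limit of 22% when no side effects are seen.

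**Cost.** Protocol and analysis-plan wording, plus agreement on the bands and the adherence minimum. No extra patients or data are needed. The downside is that the stated value of n = 15 will look less favourable.

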#### Eligibility criteria

2.2.2

Patients with any type or stage of cancer, who have reported chronic CRP (i.e., for 3 months or longer), are eligible to participate. Patients could be on active treatment, posttreatment, or receiving palliative care (see Table 1 for rationale of all inclusion and exclusion criteria).

**Table 1 T1:** Eligibility criteria.

Criteria	Rationale
Inclusion	
Chronic cancer-related pain. Specifically, one screening question will be used: “Do you have bodily pain related to cancer or as a result of cancer treatment that has lasted for more than three months?” (Answer must be yes to proceed with eligibility assessment)	This criterion is consistent with the chronic pain definition by the International Association for the Study of Pain (2).
Moderate to severe pain interference with function, as indicated by a score of >3 on the Brief Pain Inventory-pain interference with daily activities 10-point Likert scale (0 = “does not interfere” and 10 = “interferes completely”) (49)	Interventions targeting chronic pain often aim to improve both pain intensity and pain-related functional impairment (16).
Cancer diagnosis (all stages)	This criterion is intentionally broad to enhance generalizability.
Ability to speak and read in English	Mindfulness audio narrative and study assessments will be in English.
Exclusion	
Patients with dementia, Alzheimer disease, intellectual disability, amnesia, schizophrenia, psychosis, or with a history of seizures or epilepsy	People with pre-existing neuropsychological conditions may be at high risk for adverse events (e.g., confusing virtual reality with real world) (50).
Severe vision or hearing problems	This study involves prerecorded audio instructions of mindfulness techniques and a 3D virtual reality experience, requiring adequate visual and hearing ability.
Recent change (i.e., in the 2 weeks prior to study enrollment) or a planned change in opioids or antidepressants during the 6-week study period	Pain and antidepressant medications can affect pain scores during the study. While this feasibility study does not aim to evaluate efficacy, inclusion criteria are meant to be comparable to those that would be used in an efficacy trial.

### Procedures

2.3

#### Recruitment

2.3.1

The main recruitment strategy will be via oncology physician referral in the outpatient clinics of the Tom Baker Cancer Centre, a tertiary care teaching hospital affiliated with the University of Calgary (Calgary, Alberta, Canada). Social media platforms, such as Facebook, Instagram, and Twitter, and community cancer support organizations will also be used to enrich recruitment and reach underrepresented populations. The study coordinator will make a telephone call to referred patients or those who have expressed interest via advertisements to describe the purpose of the study, provide details about the intervention and the number and frequency of assessments to be completed, and screen for eligibility. Those who are interested in participating and eligible will sign an electronic consent form.

#### Baseline call

2.3.2

Consenting participants will be mailed or delivered a head-mounted VR display headset (Pico Neo 3 Pro) with the VRGM protocol preinstalled. Prior to starting the intervention, participants will complete a 20 min baseline in person or by videoconference call with the investigative team to ensure receipt of the VRGM kit and for an orientation session (e.g., how to wear and set up the headset, what are the buttons required, and what they do). After orientation, participants will complete a 15 min trial session with the study coordinator or a trained research assistant (RA) to assess how comfortable they are with the VR experience and if they develop simulator sickness, which is a possible side effect of VR (41). Simulator sickness is generally attributed to the discrepancy between simulated visual motion and the sense of movement stemming from the vestibular system, producing symptoms similar to motion sickness (41). After the trial session, participants will complete the Simulator Sickness Questionnaire (SSQ) (41) with the study coordinator or RA, a well-validated scale that assesses 16 symptoms on a 4-point scale (scores 0–3): nausea, general discomfort, stomach awareness, sweating, increased salivation, vertigo, burping, difficulty concentrating, difficulty focusing, eyestrain, fatigue, headache, blurred vision, dizziness with eyes open, dizziness with eyes closed, and fullness of head. A total SSQ score greater than 20 indicates that symptoms may be concerning (41), and thus participants may have high tendency to develop simulator sickness. Therefore, participants who score >20 on the SSQ will be deemed ineligible to proceed with study participation. They will be asked to stop using the VR headset and return it to investigators. Instead, they will be provided with resources for other mindfulness platforms.

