#### Objective 1: to evaluate the feasibility of a self-administered, at-home, 6-week VRGM program for chronic CRP

1.2.1

Feasibility outcomes include recruitment rates, intervention adherence, and study completion rates, as well as intervention safety as determined by the occurrence, type, and severity of negative side effects.

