### Feasibility evaluation

2.6

A log containing information on the number of patients approached for participation, the number referred to the research team, the number successfully contacted by the research team, and those who consented will be maintained. The number of patients who declined or did not meet the eligibility criteria and the underlying reasons will also be recorded. Another log will be maintained for the number of participants who dropped out during the study. Home practice will be tracked through engagement data from the VR device, which include session length, total time spent using the headset, and number of daily VRGM sessions. Data collected from the VR device will be verified through a daily home practice log. The log will provide space to input the date, number of VRGM sessions completed each day, total number of minutes per session, and comments about their experience and side effects. Participants will also be contacted once weekly to ask whether they have experienced any side effects. Data obtained from study logs will be used to calculate recruitment and study completion rates. Data collected from the VR system, home practice logs, and weekly emails will be used to evaluate intervention adherence and safety.

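### Participants stopped for a high SSQ score after the trial VR session are labelled ineligible, and the stated safety sources omit the SSQ, so sickness at first exposure has no route into the primary side-effect rate

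*Protocol article*

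**What the plan says.** The order of events is explicit. In Methods 2.3.1, "Those who are interested in participating and eligible will sign an electronic consent form". In 2.3.2, consenting participants receive the headset, attend orientation, complete a 15 min trial session and then the SSQ. The outcome for high scorers is that "participants who score >20 on the SSQ will be deemed ineligible to proceed with study participation"; they stop using the headset and return it. The same section describes simulator sickness as a possible side effect of VR.

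Side effects belong to the primary outcome. The Abstract states: "The primary outcome is feasibility as assessed by accrual rates, retention in the study, intervention adherence, questionnaire completion, and side effect rates". Objective 1 includes "intervention safety as determined by the occurrence, type, and severity of negative side effects".

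On data sources, 2.6 states: "Data collected from the VR system, home practice logs, and weekly emails will be used to evaluate intervention adherence and safety". On logging, the same section states: "The number of patients who declined or did not meet the eligibility criteria and the underlying reasons will also be recorded". Participants who drop out during the study go in a separate log.

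On eligibility, 2.2.2 refers the reader to Table 1 ("see Table 1 for rationale of all inclusion and exclusion criteria"), but Table 1 has no SSQ criterion. On size, 2.2.1 states: "The recruitment goal is 15 participants".

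**The concern.** The SSQ is completed after VR exposure and measures the one side effect that the article singles out as a risk of VR. A person who shows it is then classed as not eligible. If the side-effect rate is built only from the sources in 2.6, it leaves out the people in whom that side effect was most evident at first contact.

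The article says that the study will give the foundation for a larger efficacy study. Planners of that study need to know how many consenting patients cannot tolerate a first session, as well as what happens to those who can. A rate confined to the second group, presented as the side-effect rate of the intervention, would mislead them.

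**Working it through.** **Step 1. Can a post-trial SSQ score above 20 reach the side-effect rate through the listed sources?**

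- *VR system.* Section 2.6 lists session length, total headset time and number of daily sessions. Table 5 adds pain, immersion and presence ratings. None of these records symptoms.
- *Home practice log.* It has space for side effects, but Table 5 starts it in week 1. The trial session comes earlier, and a stopped participant has returned the headset.
- *Weekly contact.* It asks about side effects, but it is described alongside home practice. Nothing extends it to people stopped at the baseline call.
- *SSQ.* It is not named in 2.6, Table 4 or Table 5.

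No listed source captures the event.

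**Step 2. The plan's own figure.** The target of 15 rests on comparison with studies of 13 to 19 participants. There is no formula or assumed rate to reproduce, and no expected SSQ failure rate is given. The counts below are therefore assumptions.

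**Step 3. Formula.** Let N people be exposed, k score above 20, and s of the N − k who continue report a side effect.

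- Failures left out: s/(N − k)
- Failures counted: (s + k)/N
- Difference: k(N − k − s) / [N(N − k)]

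The difference is positive whenever k ≥ 1 and at least one continuing participant has no side effect.

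**Step 4. Fifteen exposed in total (assumed s = 2 and one later dropout).**

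| k | Side effects, failures out | Side effects, failures in | Retention, failures out | Retention, failures in |
|---|---|---|---|---|
| 0 | 2/15 = 13.3% | 2/15 = 13.3% | 14/15 = 93.3% | 14/15 = 93.3% |
| 1 | 2/14 = 14.3% | 3/15 = 20.0% | 13/14 = 92.9% | 13/15 = 86.7% |
| 3 | 2/12 = 16.7% | 5/15 = 33.3% | 11/12 = 91.7% | 11/15 = 73.3% |
| 5 | 2/10 = 20.0% | 7/15 = 46.7% | 9/10 = 90.0% | 9/15 = 60.0% |

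Check at k = 3: 3 × 10 / (15 × 12) = 16.7 points. The retention columns show only what is at stake if failures leave that denominator, which the article does not settle.

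**Step 5. Failures replaced until 15 continue (assumed no later side effects or dropouts).** Left out, side effects are 0/15 (exact 95% CI 0 to 21.8%) and retention is 15/15, whatever k is. With k = 3 counted, side effects are 3/18 = 16.7% (3.6 to 41.4%) and retention is 15/18 = 83.3%.

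**Step 6. How likely is at least one failure among 15?** The chance is 1 − (1 − p)^15. For assumed p of 5%, 10%, 20% and 30%, it is 54%, 79%, 96% and 99.5%.

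**Step 7. What if some scores reflect symptoms already present?** Suppose only m of the k failures are true VR side effects. The rate over all exposed is then (s + m)/N, and leaving failures out understates it when m/k > s/(N − k). At k = 3 and s = 2 the threshold is 2/12 = 16.7%, so one true case among the three is enough: 3/15 = 20.0% against 16.7%. If none were true, the direction would reverse: 2/15 = 13.3% against 16.7%.

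**The case against.** The best defence is that the trial session is a tolerance check. Section 2.3.2 places it before the intervention, and 2.4 defines the intervention as the six weeks of daily practice. Counting adherence from the start of that practice is a legitimate choice, since someone told to return the headset cannot be non-adherent to home sessions. This stands, and adherence should keep that base.

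A reader might infer that stopped participants certainly disappear from retention and adherence. The article does not support that. Section 2.9.1 gives no denominators, and analysis sets are commonly left to a fuller document. Section 2.6 also leaves it open which log these consented participants enter. The label of ineligible points to the first log, but that is an inference.

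A reader might also infer that every score above 20 is sickness caused by VR. No SSQ before exposure is described, the items include fatigue, nausea and headache, and eligible patients may be on active treatment or in palliative care. Some scores may reflect existing symptoms, so counting each one as a VR side effect would go too far.

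It can further be said that nothing is lost, because ineligible patients are logged with reasons, and that the study is descriptive with no threshold to cross. Both are true. But an ineligibility log does not feed the side-effect rate, and a descriptive primary outcome still has to describe the people who were exposed.

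**Conclusion.** The point holds for the side-effect rate. It rests on what the article states: exposure before the SSQ, reclassification after it, and a list of safety sources without it. The resulting rate is biased downward whenever at least one person fails and the failing scores mostly reflect the session; Step 7 gives the exact condition. The magnitude cannot be fixed from the article. Over 15 people, each failure counted moves a rate by 1/15 = 6.7 points, so even one matters.

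For retention, adherence and the target of 15, the supported conclusion is narrower: the article does not say how these participants are handled, and its wording leans toward exclusion. The absence of the rule from Table 1 is a plain inconsistency with 2.3.2. Because a primary outcome is affected and the data are already collected, this is worth correcting before results are reported.

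**What to change.** 1. In 2.6 and 2.9.1, add the post-trial SSQ to the safety data sources.
2. Report the number and proportion scoring above 20, with the symptoms, as post-exposure symptoms over all consented and VR-exposed participants. Note that some may be pre-existing, because no score before exposure is described.
3. Give side-effect and retention rates twice, each labelled: from consent or first exposure, and among those who continue. Give adherence among those who start the six-week intervention.
4. State whether the target of 15 counts consented or continuing participants, and whether stopped participants are replaced.
5. Reconcile Table 1 with 2.3.2, and state which log holds participants stopped after the trial session.

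The SSQ stopping rule does not need to change for any of this. The cost is wording and a second line in the results table, with no new data collection. The downside is that the headline feasibility figures may look somewhat less favourable.
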